##### Secondary Outcomes:

- Minute volume
- Tidal volume
- Respiratory rate
- Intertidal tracheal pressure amplitude
- Peak airway pressure
- End-tidal  $\text{CO}_2$
- Chest wall compliance
- Respiratory resistance
- Inhaled oxygen fraction ( $\text{FiO}_2$ )
- Arterial  $\text{CO}_2$  ( $\text{PaCO}_2$ )
- Tube obstruction by secretion

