Evone® is the only commercially available ventilator applying FCV ventilation mode, thus directing the inspiration as well as the expiration [Figure 2]. Evone's FCV® ventilation mode is based on a controlled inspiration and expiration flow from a set PEEP to a set peak pressure and vice versa. The inspiratory flow is continuously controlled by advanced mass flow regulators; the expiratory flow is controlled by regulated suctioning.

[figure not shown]

Figure 2: Evone, Ventinova Medical, Eindhoven, The Netherlands

Evone is to be used in combination with Tritube [Figure 3], an ultra-thin endotracheal tube (outer diameter 4.4 mm/ inner diameter 2.4 mm), enabling highly accurate intra-tracheal pressure measurements and securing the airway with an inflatable high volume – low pressure cuff because FCV ventilation requires a sealed airway. With an outer diameter (OD) of only 4.4 mm, Tritube® is an ultra-thin ventilation tube, intended to obtain endotracheal access to the airway and to ventilate an adult patient [Figure 3]. Tritube has three lumina: a ventilation lumen - with Murphy eye and an inner diameter (ID) smaller than 3 mm; a cuff lumen - to inflate and deflate the high volume, low pressure cuff; and an intra-tracheal pressure measurement lumen - for continuous intra-tracheal pressure measurements. Tritube (including its cuff) is completely manufactured of Polyurethane. Additionally, Tritube has a malleable stylet to facilitate intubation [8, 9].

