## 5. Variables

We will collect demographic data (age, sex, BMI), co-morbidities and clinical data (need for special intervention, e.g. “proning”) drugs used and fluids administered.

Next to the vital parameters (blood pressure, heart frequency and body temperature) the oxygenation parameters (BGA) will be collected 6-8 hourly according to clinical standard.

Kidney-function parameters (creatinine, urea), liver function tests and whole blood counts and immune-parameters like interleukin 6 (IL-6) will be recorded.

Cardiac enzymes will be collected (troponin, BNP) will be evaluated and reported on clinical need.

All of these parameters are reported routinely on daily base for clinical purpose.

Demographic parameters:

- Age
- Gender
- Body Mass Index (BMI)
- Co-morbidities
- Drug history

Laboratory parameters (routinely sampled):

- Coagulation parameters (aPTT, INR/PT, fibrinogen levels, D-dimer)
- Whole blood count (including differential blood count)
- Metabolic parameters (Creatinine level, LDH, liver function tests, albumin level)
- Lactate level
- CRP, IL-6
- Troponin

Clinically parameters:

- Timing of clinical course (e.g. admission, ICU admission, intubation, ECMO)
- Time of intubation
- Time to extubation
- SOFA score

The following respiratory parameters will be recorded together with the BGA (6-8 hourly):

- Pressure during inspiration (PIP)
- Positive End-Expiratory Pressure (PEEP)
- Lung compliance
- Minute volume
- Tidal volume
- Respiratory rate (RR)
- Intratracheal pressure amplitude
- Peak airway pressure
- End-tidal CO2
- Chest wall compliance
- Respiratory resistance
- FiO2

- I: E ratio
- ABG

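### Chest wall compliance is a secondary outcome listed separately from lung compliance, but with only airway-side pressures recorded neither can be separated from respiratory-system compliance

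*Protocol*

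**What the plan says.** Section 4 of the protocol lists eleven secondary outcomes. One is "Chest wall compliance". Neither lung compliance nor respiratory-system compliance is among them.

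Section 5 introduces its respiratory list with "The following respiratory parameters will be recorded together with the BGA (6-8 hourly"). "Lung compliance" is the third item and chest wall compliance the tenth, so the protocol treats them as two quantities. Neither is defined, and respiratory-system compliance is not named anywhere.

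The pressures in the same list are inspiratory pressure, PEEP, "Intratracheal pressure amplitude" and "Peak airway pressure". Tidal volume is also recorded. For the study tube, section 3 describes "an intra-tracheal pressure measurement lumen - for continuous intra-tracheal pressure measurements". Section 6 states no pressure-measurement site for group B. No pleural or oesophageal pressure is described for either group.

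**The concern.** Chest wall compliance is the volume change divided by the change in pleural pressure. Lung compliance is the volume change divided by the change in airway pressure minus pleural pressure. Both need a pressure that the protocol does not plan to record. Airway pressures with tidal volume describe the lung and chest wall together.

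A named secondary outcome may therefore have no valid value. Or it may be filled with a single compliance figure from the ventilator or chart, which would be respiratory-system compliance. In the second case a change in the lung would appear as a change in the chest wall. This matters for interpretation because section 3 places the expected benefit of flow-controlled ventilation in small airways and alveoli that stay open, which is a lung mechanism.

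A statistical analysis plan could not repair this later. It can define how a quantity is computed, but it cannot supply a pressure that was not recorded.

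**Working it through.** The protocol states no figure on this point, so there is nothing to reproduce. The check is whether the recorded data identify the named quantities.

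**Inputs from the protocol (section 5):** tidal volume (VT), inspiratory pressure, PEEP, intratracheal pressure amplitude and peak airway pressure. Pleural pressure: none.

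**Definitions**, with ΔPaw the change in airway pressure and ΔPpl the change in pleural pressure:
- respiratory system: Crs = VT / ΔPaw
- lung: CL = VT / (ΔPaw − ΔPpl)
- chest wall: Ccw = VT / ΔPpl

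The elastances (reciprocals) add: 1/Crs = 1/CL + 1/Ccw. The compliances themselves do not add.

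**Identifiability.** VT and ΔPaw fix Crs. That leaves one equation with two unknowns, CL and Ccw. As an illustration with assumed values that are not in the protocol, take VT = 420 ml and ΔPaw = 14 cmH2O, so Crs = 420/14 = 30 ml/cmH2O. Let f be the lung's share of total elastance. Then CL = 30/f and Ccw = 30/(1 − f).

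| Assumed f | CL | Ccw | Ccw / Crs |
|---|---|---|---|
| 0.6 | 50.0 | 75 | 2.5 |
| 0.7 | 42.9 | 100 | 3.3 |
| 0.8 | 37.5 | 150 | 5.0 |
| 0.9 | 33.3 | 300 | 10.0 |

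All four rows have the same tidal volume, the same airway pressures and the same Crs. The recorded data cannot tell them apart.

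**Size of the error if Crs were labelled chest wall compliance.** Assume CL = 40 ml/cmH2O:
- Ccw = 100: Crs = 1/(1/40 + 1/100) = 28.6, and 100/28.6 = 3.5
- Ccw = 150: Crs = 1/(1/40 + 1/150) = 31.6, and 150/31.6 = 4.75
- Ccw = 200: Crs = 1/(1/40 + 1/200) = 33.3, and 200/33.3 = 6.0

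**Attribution of a treatment effect.** Suppose flow control raised CL from 40 to 50 with Ccw fixed at 150. Crs would go from 31.6 to 1/(1/50 + 1/150) = 37.5, a rise of 37.5/31.6 − 1 = 19%. Under the chest wall label this would read as a 19% improvement, while the true chest wall change is zero.

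**Limit on Crs itself.** The list contains no plateau or other zero-flow pressure. If the inspiratory pressure contains a resistive part r, the computed value is VT/(ΔPaw + r), which is below VT/ΔPaw. Group A pressure can be sensed in the trachea, and section 3 describes flow there as continuous, without pauses. For group B neither the measurement site nor a zero-flow manoeuvre is stated. The resistive part could therefore differ between arms.

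**The case against.** The strongest reply is that the protocol says these parameters will be recorded, not that they will be derived from the listed airway pressures. The data collection sheet is an appendix that is not shown and may say how each value is obtained. The derivation of a secondary variable is also often left to the statistical analysis plan. And this is one of eleven unranked secondary outcomes in a 20-patient feasibility study.

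Part of this stands. A reader might infer that the trial will report respiratory-system compliance under the name of the chest wall. The protocol does not say so. It is a likely consequence of the two lists, and confidence in what a site would enter should be limited accordingly. A reader might also infer that section 4 pairs the two compliances. It does not: lung compliance appears only in section 5, and not next to chest wall compliance. The numerical illustrations rest wholly on assumed compliances.

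It is also fair that simply dividing tidal volume by inspiratory pressure minus PEEP in both arms is not enough. The same formula can give different quantities when the measurement site and flow conditions differ, and the difference could look like a treatment effect.

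The mismatch itself remains. The protocol fixes both the outcome and the list of recorded pressures, and the second cannot produce the first. If no compliance figure were entered at all, the secondary outcome would still go unanswered.

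**Conclusion.** The concern holds as a mismatch between a named secondary outcome and the recorded data. Neither chest wall nor lung compliance can be separated from the pressures that the protocol lists. Any single compliance figure from the ventilator or chart would be respiratory-system compliance, and only approximately so without a zero-flow pressure.

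Under the assumed compliances, reading that figure as chest wall compliance would understate it by a factor of 3.5 to 6 (2.5 to 10 over the assumed elastance shares). It could also show a 19% change where the true change is zero. These figures indicate direction and order of size. They are not estimates for this trial.

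A reader might go further and conclude that the trial's main result is compromised. The protocol does not support that: the primary endpoint is PaO2, and neither it nor the sample size depends on any compliance. The change should be made, but it is not critical to the trial's main question.

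**What to change.** In sections 4 and 5 and on the data collection sheet, replace chest wall compliance and lung compliance with one outcome, respiratory-system compliance. Specify that:
- it is tidal volume divided by (end-inspiratory pressure minus PEEP), from the values recorded with each blood gas;
- the pressure used and its measurement site are named for each arm;
- it is labelled dynamic (approximate) where no zero-flow pressure is available, with a note that a difference in measurement site or flow could create an apparent difference between arms;
- no separate conclusion is drawn on the lung or the chest wall.

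If the investigators do intend to measure pleural pressure, the protocol should instead say how it is obtained in both arms.

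The renaming is a wording change in two lists and on the data sheet, with no added procedure. It gives up one nominal outcome that could not be measured as planned. It should be made before data collection, because a single compliance figure entered under either name cannot be split into its components afterwards.

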## 5. Variables

We will collect demographic data (age, sex, BMI), co-morbidities and clinical data (need for special intervention, e.g. “proning”) drugs used and fluids administered.

Next to the vital parameters (blood pressure, heart frequency and body temperature) the oxygenation parameters (BGA) will be collected 6-8 hourly according to clinical standard.

Kidney-function parameters (creatinine, urea), liver function tests and whole blood counts and immune-parameters like interleukin 6 (IL-6) will be recorded.

Cardiac enzymes will be collected (troponin, BNP) will be evaluated and reported on clinical need.

All of these parameters are reported routinely on daily base for clinical purpose.

Demographic parameters:

- Age
- Gender
- Body Mass Index (BMI)
- Co-morbidities
- Drug history

Laboratory parameters (routinely sampled):

- Coagulation parameters (aPTT, INR/PT, fibrinogen levels, D-dimer)
- Whole blood count (including differential blood count)
- Metabolic parameters (Creatinine level, LDH, liver function tests, albumin level)
- Lactate level
- CRP, IL-6
- Troponin

Clinically parameters:

- Timing of clinical course (e.g. admission, ICU admission, intubation, ECMO)
- Time of intubation
- Time to extubation
- SOFA score

The following respiratory parameters will be recorded together with the BGA (6-8 hourly):

- Pressure during inspiration (PIP)
- Positive End-Expiratory Pressure (PEEP)
- Lung compliance
- Minute volume
- Tidal volume
- Respiratory rate (RR)
- Intratracheal pressure amplitude
- Peak airway pressure
- End-tidal CO2
- Chest wall compliance
- Respiratory resistance
- FiO2

- I: E ratio
- ABG

## 6. Study Methodology:

This is a prospective, randomized feasibility study in adult patients with proven COVID-19 associated ARDS. We define ARDS according to “Berlin” definition integrating the oxygenation index (P/F ratio), the level of PEEP and clinical findings [3, 4].

We will use an envelope method to randomize patients into the flow-control ventilation group (group A) while all other patients will receive standard treatment (pressure control ventilation-group B). Due to the nature of the investigation (we use a special device and tube) blinding of the study groups will not be possible. The study will be performed in HMC facilities hosting COVID-19 patients.

After admission to the ICU for COVID-19 associated respiratory disease, the patients (or their relatives) will be approached, informed about the study and if agreed informed consent will be taken. Upon intubation the severity of the disease will be assessed thrice daily. When the patient fulfils the criteria for moderate to severe ARDS (P/F ratio between 100mmHg and 200 mmHg with PEEP of minimal 5 cmH2O and below 100mmHg with a minimal PEEP 5 cmH2O, respectively) randomization will be performed. Hereafter the group A patients will receive the ultra-thin Tritube through the existing tube. This does not need exchange of the tube, so it does not generate additional risks for the staff in terms of aerosols.

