## **9. Statistical Consideration and Data Analysis**

Power-calculation: In order to keep the total number of patients small we will match the patients according to age, co-morbidities inhaled oxygen fraction and we regard this investigation as a feasibility study. Therefore, the sample size calculation based on the assumption of an effect size (change in PaO2) of 1.5 SDS in the primary endpoint (PaO2), an intended power of 80%, an alpha error of 5% and an equal sample ratio results in n=7 patients needed to treat. However, to compensate for dropouts we will include 10 patients in each group, which means in total 20 patients.

Data analysis: Categorical data will be presented as number and percentage, while interval data will be presented by median and interquartile range (IQR). Normally distributed data will be analyzed by using two-tailed unpaired Students t-test. Continuous variables with skewed distribution will be analyzed using Mann-Whitney U testing and dichotomous variables by means of Fisher's exact test. A p-value <0.05 is considered significant. All data analyses will be done using SPSS version v26 (IBM Corp, Armonk NY, USA). Graphs will be constructed using GraphPad Prism (GraphPad Prism version 5.0a for Windows, GraphPad Software, San Diego CA, USA).

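### Moderate and severe ARDS are enrolled together, but neither the stated allocation nor the unadjusted primary test uses the P/F ratio known at randomization

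*Protocol*

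**What the plan says.** Section 6 (Study Methodology) assesses severity three times a day after intubation and randomizes once the criteria for moderate or severe ARDS are met: "P/F ratio between 100mmHg and 200 mmHg with PEEP of minimal 5 cmH 2 O and below 100mmHg with a minimal PEEP 5 cmH 2"O. The P/F value is therefore in hand when the envelope is opened. Allocation is described only as "We will use an envelope method to randomize patients into the flow-control ventilation group (group A"), with the remaining patients receiving pressure-controlled ventilation. No strata, blocks or minimization factors are given.

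Section 9 (Statistical Consideration and Data Analysis) says that, to keep the trial small, "we will match the patients according to age, co-morbidities inhaled oxygen fraction". The sample size assumes "an effect size (change in PaO 2 ) of 1.5 SDS in the primary endpoint" and "an intended power of 80%, an alpha error of 5"%, from which "an equal sample ratio results in n=7 patients needed to treat". The final number is set as follows: "to compensate for dropouts we will include 10 patients in each group, which means in total 20 patients". Normally distributed data go to a two-tailed unpaired t-test and skewed data to a Mann-Whitney test. No baseline covariate enters either test. The primary endpoint in sections 1 and 4 is PaO2.

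**The concern.** PaO2 is the numerator of the ratio that defines the two entry classes, so the class at entry plausibly predicts PaO2 after randomization. It may also predict whether a patient's study period ends before 48 hours because of prone positioning or ECMO (section 6, Group B). With 20 patients, an uneven split of the classes would be hard to tell from an effect of the ventilation mode, in either direction.

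The protocol relies on baseline balance to justify its small size, yet its three statements do not fit together:

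- Section 9 matches patients.
- Section 6 randomizes them by envelope as they qualify.
- The section 9 tests are unpaired and take no account of matching.

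The matching factors also omit the P/F ratio. This is more than detail left to a statistical analysis plan, because section 9 fixes the unadjusted test and an allocation scheme cannot be changed after patients have entered.

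**Working it through.** **Inputs from the protocol.** 20 patients, 10 per arm, 1:1; effect 1.5 SD; power 80%; alpha 5%, two-tailed (section 9). Two eligible P/F classes and envelope allocation with no strata stated (section 6).

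**Assumptions, not in the protocol.** The share of severe patients, 20% to 50%. The PaO2 difference between classes, 0.5 to 1.5 SD.

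**1. The plan's own figure.** n per group = 2 × (1.960 + 0.842)² / 1.5² = 6.98, so 7, with normal-approximation power of 80.1%. The stated 7 is reproduced. Raising 7 to 10 allows for 30% dropout. The point here does not dispute this number.

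**2. Chance imbalance for a given number K of severe patients.** With 10:10 allocation, the severe count in group A is hypergeometric (20 patients, K severe, 10 drawn). Worked example for K = 8: a difference of 4 or more means 2, 1 or 0 severe patients in one arm. The probability is 2 × (13,860 + 1,760 + 66) / 184,756 = 17.0%.

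| K severe of 20 | P(difference ≥ 4) |
|---|---|
| 3 or fewer | 0% |
| 4 | 8.7% |
| 5 | 3.3% |
| 6 | 14.1% |
| 7 | 5.7% |
| 8 | 17.0% |
| 9 | 7.0% |
| 10 | 17.9% |

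The values are symmetric above 10. When K is odd, a difference of exactly 4 cannot occur, so the event means 5 or more and is rarer.

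**3. Averaged over a random K.** Take the severe counts in the arms as two independent Binomial(10, q) variables.

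| Severe share q (assumed) | P(difference ≥ 4) | P(difference ≥ 3) |
|---|---|---|
| 20% | 4.8% | 16% |
| 30% | 8.5% | 22% |
| 40% | 10.8% | 25% |
| 50% | 11.5% | 26% |

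**4. Size of the shift.** A 4-patient difference is 4/10 = 0.4 in the proportion severe. The shift in the mean contrast is 0.4 × 0.5 = 0.2 SD to 0.4 × 1.5 = 0.6 SD, which is 0.2/1.5 = 13% to 0.6/1.5 = 40% of the planned effect. The standard error of the contrast is √(2/10) = 0.45 SD, so the shift is about 0.4 to 1.3 standard errors.

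**5. Effect on the test.** In a simulation with no treatment effect and a 6-versus-2 split held fixed, the unadjusted t-test rejects in about 6%, 10% and 13% of trials at class differences of 0.5, 1.0 and 1.5 SD, mostly in the direction of the imbalance. When 8 severe patients are instead allocated at random 10:10, the rejection rate is 5.0% at all three differences. The test therefore holds its level over all allocations and misleads only within an unlucky one.

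**6. Precision.** With a 40% severe share and class difference d in within-class SDs, class adds 0.4 × 0.6 × d² = 0.24d² to the variance. As a share of the total this is 0.06/1.06 = 6%, 0.24/1.24 = 19% and 0.54/1.54 = 35% at d = 0.5, 1.0 and 1.5. Adjustment for class can remove that part.

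**7. Does matching on inhaled oxygen fraction cover it?** Only in part. At an inhaled fraction of 0.6 (illustrative), a PaO2 of 55 mmHg gives P/F 92 and a PaO2 of 75 mmHg gives P/F 125. These are different classes at the same inhaled fraction.

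**The case against.** The strongest reply is that chance imbalance after randomization is not bias. The error rate of the t-test already allows for it, and the 0.2 to 0.6 SD shift lies within the sampling error instead of adding to it. Step 5 confirms this, so a reader who infers that the comparison is invalid goes too far.

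Other objections also stand, at least in part:

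- A reader might take 14% to 18% as the chance of a 4-patient imbalance. That range holds only for even totals from 6 to 14 severe patients, and the protocol gives no severe share. Section 7 excludes patients who need prone positioning or ECMO, which may lower it.
- A reader might infer that nothing is done about severity, or that there is one unstratified set of envelopes. The protocol claims matching on inhaled oxygen fraction, which is part of P/F, and does not say how the envelopes are organized.
- A reader might infer that the exclusions in section 7 leave almost no co-morbidity to match on. They name chronic respiratory and cardiovascular disease and limit BMI, and leave, for example, diabetes and renal disease eligible.
- Section 9 describes the effect as a change in PaO2. Analysing change would remove some of the baseline difference, but sections 1 and 4 name PaO2 itself and no change analysis is specified.
- Not stratifying a 20-patient feasibility study is a defensible choice.

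None of this explains why the analysis should ignore a prognostic value that every patient must have measured to enter.

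**Conclusion.** The point holds as a weakness of design and analysis. The protocol mixes two severity classes, states no allocation by class, names matching factors that cover P/F only in part and cannot be applied as described, and fixes a test that uses no baseline value.

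A severe-count difference of 4 or more has an average probability of about 5% to 12% for an assumed severe share of 20% to 50%. Conditional on the total it ranges from 0% to 18%. The shift of 13% to 40% of the planned effect rests on the assumed 0.5 to 1.5 SD difference between classes. The harm is lost precision and a result that is harder to interpret. The documents do not support a claim of bias or of an inflated overall error rate.

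**What to change.** **Main change, section 9.** Replace the unadjusted primary comparison with an analysis of covariance of PaO2 on treatment and the qualifying, pre-randomization P/F ratio, preferably as a continuous covariate. The value is already measured for eligibility. The cost is one residual degree of freedom (18 to 17 with 10 per arm), and the planned number of patients does not change. If P/F turns out to be only weakly related to later PaO2, the gain will be small.

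**Optional change, section 6.** In place of the matching, prepare two envelope sets, P/F below 100 and 100 to 200, each in small permuted blocks of varying size. Blocks of 2 hold the severe-count difference to at most 1 and blocks of 4 to at most 2, so a difference of 4 cannot arise. There are two costs. Allocation becomes somewhat more predictable in an unblinded trial. With blocks of 2 and 4, each of the two strata can end 2 out of balance, so the arms could finish 12 versus 8 instead of 10 each.

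**In either case.** Reconcile the matching in section 9 with the envelope randomization in section 6 and the unpaired tests: either delete the matching, or describe a procedure that works for patients entering one at a time and an analysis that reflects it.
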